### Recruitment

Participants will be enrolled into the trial over a 27-month recruitment period, yielding a rate of ~16 participants/month. The planned enrollment period will begin January 2013 and conclude in April 2015. Women will be enrolled in consecutive “waves” of ~n=50 for efficient use of personnel and resources across the study period and to test women close to the start and end of exercise classes. The primary method of recruitment will be through mailings from the Oregon State Cancer Registry (OSCaR), a population-based tumor registry run by the Department of Human services that collects and analyzes information on cancer cases in Oregon. The registry will send an information letter to all living female cancer survivors with eligible diagnoses, between the ages of 50 and 75 years old and within a 30 mile radius of the intervention sites that describes the study and asks them to return a pre-paid response form indicating their willingness to be contacted. Additional recruitment strategies include direct referral through oncology providers at OHSU and other local clinics and direct community recruitment using newspaper ads, radio, announcements on websites, as well as presentations at cancer support groups and cancer-related conferences.

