### Study interventions

Participants in each study group will attend supervised 1-hr classes, twice weekly for 6 months. It is expected that women with mixed employment status will enroll in the study so daytime and early evening classes will be offered. At each site, a certified exercise instructor trained by the study team will lead classes. Each intervention minimizes reliance on expensive equipment and uses simple, easily performed exercises based on functional movements. It is difficult to precisely equilibrate the total volume (intensity and duration) of exercise performed between experimental groups because the nature of each modality is so different. Both will be matched as closely as possible in progression from the low to high end of the range for moderate intensity. Instructors will work with the study investigators and project director on a monthly basis to refine individual participant efforts based on individual tolerance and to adjust their training progression.

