### Stretching control

Participants in the control group will attend a supervised stretching program of the same frequency, duration, and length as the tai chi and strength training groups. During stretching, participants will perform a series of whole body flexibility (stretching) and progressive neuromuscular relaxation exercises. Stretching exercises will be performed according to the ACSM guidelines for flexibility exercise: static stretching that emphasizes major muscle groups with 3–4 repetitions of each stretch held to the point of mild tension but not pain for 10–30 seconds [52]. Stretches will be performed from a seated or lying position in order to minimize weight-bearing forces that might increase muscle strength or postural control. The stretching will also be limited in duration to 15–20 minutes, with the remainder of the class devoted to relaxation exercises that produce no neuromuscular stimulus. Many exercise trials in older adults, including ours and including studies with falls as an outcome, have used a flexibility training control condition and results have shown no effect of this training on outcomes associated with tai chi or strength training [36,53-56]. A recent ACSM Roundtable issuing exercise guidelines for cancer survivors recommended “avoidance of inactivity” among cancer survivors to optimize quality of life [46]. Stretching and relaxation exercise increases range of motion, promotes a sense of wellbeing and may be viewed as a beneficial exercise program for participants randomized to this group. We are including a measure of flexibility in our list of outcomes in order to assess the potential benefit of the stretching program and provide an incentive to participants in this group by including a measure that could improve from stretching exercise.

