### Data analysis plan

The univariate distribution of each variable will be examined to check for departure from normality and outliers [76]. For each analysis described below, each subject will be analyzed according to the group to which she was randomly assigned and regardless of missing data (i.e., intention to treat). Medical treatment changes and cancer recurrence during the study will be tracked and used to describe the sample and document why participants may not have completed the study. In the unlikely event of a large subgroup, these data could be used for exploratory sub-group analysis to suggest directions for future research. Age, cancer type (breast or other), and time since cancer treatment completion, will be included as covariates in all analyses.

A negative binomial regression model will be used to test the efficacy of tai chi and strength training (versus stretching control) in reducing the total number of falls per participant that occur during the intervention period (from baseline to 6 months). Negative binomial regression is preferred over Poisson regression for modeling the count data because of the overdispersion that is common with actual research data [40,77]. Intervention type will be entered into the model as 2 dummy vectors, with the reference group being the control group. Fall rates for participants who drop out of the study will be adjusted by accounting for their exposure time within the study timeframe. A significant incidence rate ratio (IRR) less than 1.0 for the dummy vector representing tai chi and/or strength training would provide support for the hypothesis that the respective intervention reduced the rate of falls compared to the control group (controlling for covariates).

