Maximizing participant retention is a primary goal for conduct of the trial. Retention rates in prior exercise studies of similar length by the investigative team and in a similar population are strong (82%-85%).^21, 79^ and similar retention strategies are used for the GET FIT trial and include the following: 1) regular participant phone contact during the study 2) reserved parking place near the OHSU School of Nursing for testing appointments 3) free and close-in parking to exercise classes (as close as 200m for physically limited participants) 4) public transportation costs covered for participants who choose not to drive, 5) $10 remuneration at the end of each measurement appointment as a token of thanks, 6) allocation of every participant to an exercise program, including control group participants, 7) offering exercise classes at various community locations in the study area, and 8) encouragement of group cohesion by promoting social interaction through activities inside and outside of class (i.e., holiday potlucks, coffee/tea dates, team building activities during classes).

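### All three arms are taught in classes, but the primary falls model and the sample size make no allowance for clustering by class; if women in a class are correlated, the error rate exceeds 5% and power falls below 80%.

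*Protocol article*

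**What the plan says.** **Delivery.** Study interventions: "Participants in each study group will attend supervised 1-hr classes, twice weekly for 6 months". The Stretching control section adds: "Participants in the control group will attend a supervised stretching program of the same frequency, duration, and length as the tai chi and strength training" arms. The three programmes differ in content, so each class belongs to one arm and classes are nested within arm. This is an inference from the design; the article does not say it outright. On staffing it says only "At each site, a certified exercise instructor trained by the study team will lead classes".

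**Reasons to expect some correlation.** Among the retention measures in the Discussion is "encouragement of group cohesion by promoting social interaction through activities inside and outside of class". The Discussion also accepts that delivery could be inconsistent across sites. It answers this with instructor training, written guidelines and a supervisor who observes classes every two weeks.

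**Primary analysis.** Data analysis plan: "A negative binomial regression model will be used to test the efficacy of tai chi and strength training (versus stretching control". The outcome is the "total number of falls per participant that occur during the intervention period (from baseline to 6 months". Treatment enters as two dummy vectors with control as reference, and drop-outs are handled through exposure time. The covariates are fixed: "Age, cancer type (breast or other), and time since cancer treatment completion, will be included as covariates in all analyses". No class term and no clustered variance is named.

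**Sample size.** Power and sample size lists alpha .05, R² = .25 and phi = 2.5, giving 342 analysed women (114 per group) for 80% power, raised to 429 randomized. It states no ICC, class size or design effect.

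**The concern.** Women are randomized one by one, so baseline differences between them average out across arms. What happens in a class after randomization does not average out in the same way. A class that coheres well, or is taught at a harder pace, shifts the fall rate of several women in one arm together. That shared variation adds to the variance of the arm comparison. A negative binomial model with only the listed terms sets it to zero. The overdispersion parameter does not replace it, because that parameter describes variation between individual women and not variation they share.

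At stake are the width of the confidence intervals for the two primary rate ratios, the 5% error rate of the tests on them, and the power claim.

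**Working it through.** **The plan's own figure.** I used the usual Poisson-regression formula with an overdispersion factor: N = phi × (z_a√V0 + z_b√V1)² / (T × rate × ln(RR)²) / (1 − R²). Inputs: RR = 0.53, phi = 2.5, R² = 0.25, T = 1 year, two-sided 5%, 80% power, one exercise arm as one third of the sample. Then V0 = 1/(1/3 × 2/3) = 4.5, V1 = 1.5 + 3/0.53 = 7.16, the squared bracket is 41.09 and ln(0.53)² = 0.403.
- Control rate 0.30 falls per year (reading the quoted 30% who fall as a rate): 2.5 × 41.09 / (0.30 × 0.403) / 0.75 ≈ 1,133.
- Control rate 1.0 per year: ≈ 340, close to 342.

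So 342 is reached only with a control rate that the article does not state, and no variant that reaches it contains a design effect. Below, the nominal 80% at 342 is taken at face value.

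**Class size (bounded, not given).** Women enter in waves "of ~n=50 for efficient use of personnel and resources across the study period". 429/50 = 8.6, so about 9 waves. With one class per arm per wave, that is 143/9 = 15.9 randomized or 114/9 = 12.7 analysed women per class, and about 9 classes per arm. Several locations and both daytime and evening sessions point to smaller classes; 6 is taken as a small-class case.

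**Formulas**, with m = class size:
- Design effect DE = 1 + (m − 1) × ICC
- Actual two-sided error of the unclustered model = 2 × (1 − Φ(1.96/√DE))
- Power of a correctly computed test = Φ(2.802/√DE − 1.96)
- Analysed women needed for 80% = 342 × DE

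| m | ICC (assumed) | DE | SE understated by | Error | Power | Analysed N for 80% |
|---|---|---|---|---|---|---|
| any | 0 | 1.00 | 0% | 5.0% | 80% | 342 |
| 6 | 0.01 | 1.05 | 2.4% | 5.6% | 78.1% | 360 |
| 6 | 0.02 | 1.10 | 4.7% | 6.2% | 76.2% | 377 |
| 12.7 | 0.01 | 1.12 | 5.4% | 6.4% | 75.5% | 382 |
| 12.7 | 0.02 | 1.23 | 10.0% | 7.8% | 71.3% | 422 |
| 12.7 | 0.05 | 1.58 | 20.5% | 11.9% | 60.5% | 542 |

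The error reaches 10% when 1.96/√DE = 1.645, that is DE = 1.42. With m = 12.7 this is ICC = 0.42/11.7 = 0.036, or about 0.04. With m = 6 it is 0.42/5 = 0.084.

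**Simulation check.** Negative binomial fits ignoring class were run on null data with a class effect, 2,500 runs per setting. Here the control mean is 0.3 falls:

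| Classes per arm | ICC 0 | 0.009 | 0.017 | 0.042 | 0.080 |
|---|---|---|---|---|---|
| 9 of 13 | 4.5% | 6.1% | 8.6% | 11.6% | 17.7% |
| 18 of 7 | 4.9% | 5.6% | 7.1% | 8.3% | 11.4% |

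At ICC 0 the planned model held its level in every setting tried (4.5% to 5.9%), so the excess comes from clustering. The simulated error was mostly at or slightly above the formula. At a control mean of 0.6 with 9 classes of 13, for example, it was 9.5% at ICC 0.023, against 8.3% by formula. The fitted overdispersion did not absorb the class effect.

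**The case against.** **A condensed article.** Variance estimation and random effects are often left to a full analysis plan, which is not at hand. The article does not say that its listed terms are the only ones. This stands as a caveat: an unseen plan may already handle clustering. But the article fixes the model family, coding, reference group, covariates and exposure handling, and a reader who follows it fits a model with no class effect. The sample-size inputs leave clustering out as well.

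**The excess error is conditional.** A reader might infer that the 5% rate is definitely not held. The documents do not support that: no ICC is given, and at zero the model is valid. The instructor training and supervision also aim to reduce the very variance at issue.

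**Wave, season and site.** A reader might also infer that a bad season or one site's results could pass for an effect of exercise type. This does not follow. Women are randomized individually and each wave can be expected to contain all arms, so effects shared by the arms do not make the standard error of the arm contrast too small. Only effects nested within arm count. Nor does the article say that instructors are arm-specific; one who teaches several programmes is at least partly crossed with arm. The point therefore rests on the class.

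**Class size.** Several sites and session times make large classes less likely. Against this, drop-outs stay in the model with their exposure time, so the effective size could exceed 12.7. At m = 16 the error would be 6.8% at ICC 0.01 and 8.6% at 0.02.

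**Conclusion.** The point holds in conditional form. As written, the primary model and the sample size treat women taught together as independent. If the within-class ICC is above zero, the intervals for both primary rate ratios are too narrow and the error rate exceeds 5%.

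Under ICCs of 0.01 to 0.02 and classes of about 6 to 13, the excess is modest: an error of about 5.6% to 7.8%. It passes 10% only with a stronger class effect, about 0.04 with classes near 13 by formula, and somewhat lower in simulation at higher fall rates. The power loss matters as much: with classes near 13, from a nominal 80% to about 75% at ICC 0.01 and 71% at 0.02.

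The ICCs are assumptions, the class sizes are bounded from the wave size, and the nominal 80% is accepted although its baseline rate is unstated.

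**What to change.** - Fit the primary 6-month falls model with a random intercept for exercise class. Alternatively, use class-clustered standard errors with a small-sample correction, which is needed because there may be as few as about 9 classes per arm.
- Report the estimated class variance.
- Record class membership for each woman. The article says the attendance logs track adherence; if they do not also identify the class, add it.
- State in the sample-size section that the 80% power assumes no class clustering, preferably with an ICC range and its design effect.
- For the 6-to-12-month falls model, use the same approach as a sensitivity analysis, since class effects may fade once classes stop.

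**Cost.** The change is to analysis wording, plus one data item if class is not already recorded. Intervals widen and some nominal power is lost: little if the ICC is near zero, more if it is not (about 61% power at ICC 0.05 with classes near 13). That lower figure would be the trial's real precision, which the unclustered model would hide.

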Maximizing participant retention is a primary goal for conduct of the trial. Retention rates in prior exercise studies of similar length by the investigative team and in a similar population are strong (82%-85%).^21, 79^ and similar retention strategies are used for the GET FIT trial and include the following: 1) regular participant phone contact during the study 2) reserved parking place near the OHSU School of Nursing for testing appointments 3) free and close-in parking to exercise classes (as close as 200m for physically limited participants) 4) public transportation costs covered for participants who choose not to drive, 5) $10 remuneration at the end of each measurement appointment as a token of thanks, 6) allocation of every participant to an exercise program, including control group participants, 7) offering exercise classes at various community locations in the study area, and 8) encouragement of group cohesion by promoting social interaction through activities inside and outside of class (i.e., holiday potlucks, coffee/tea dates, team building activities during classes).
